### Sample size and power, data monitoring and statistical analysis

#### Sample size and power

Although cognitive outcomes have been of secondary interest in music interventions in dementia so far,^11^ there is some research to suggest a plausible effect size. Our systematic review found a mean d=0.29 (95% CI 0.02 to 0.57) of active music therapy on global cognition, based on 3 RCTs (total 209 participants); in contrast, no effects were found for music listening.^42^ A study of group-based singing found similar effects.^43^ Analyses in the Cochrane review did not distinguish between active and listening interventions.^12^ The ADAS-cog was only used in one included study,^12^ although it is more sensitive than the MMSE^44^ and has a defined MCID.^39^ With a conservative assumption of SD=10 (a large sample had SD=6.42),^44^ the MCID of 3 corresponds to an effect size of d=0.30, similar to our previous review.^42^ We further assume a within-subject correlation of r=0.5 between intervention periods; this reflects a conservative and plausible estimate of consistency across repeated cognitive assessments in this population and is consistent with recommended practice in crossover trial planning.^45^ Together with an assumed attrition rate ≤20%, and aiming for 80% power with a two-sided 5% significance level, this leads to a required number of 113 participants to randomise (90 after drop-out). Similar power would be reached for slightly smaller d and higher r or vice versa; a higher power is used if the SD is smaller. In contrast, a parallel trial would require 440 participants to achieve the same power for the same effect size. Recruitment and follow-up rates as well as data quality will be monitored and discussed with the DSMC to ensure target sample size and power.

#### Statistical analysis

Sociodemographic and diagnostic features will be analysed via descriptive methods (mean (SD), range, n (%)). Outcomes will be analysed on an intention-to-treat basis (analysing all participants as randomised, regardless of actual participation), which provides a conservative estimate of effects, and additionally on a per-protocol basis (analysing participants according to their actual participation in the trainings). We estimate that participants need to receive around 90% of the sessions during intensive musical training intervention for learning effects to occur. Multiple imputation will be used if attrition is higher than expected. Continuous outcomes will, following a graphical examination of normality, compare the post-test difference between interventions within each participant, adjusted by the difference in pre-tests within each participant in a hierarchical ANCOVA model with participant and site as random effects. The ANCOVA model ensures optimal use of baseline measures to improve precision and avoids bias from randomly occurring baseline imbalance.^46^ The model can be written as (*Y_Ti_ – Y_Ci_) = β_T_ + γ(X_Ti_ – X_Ci_*), where *Y* is the post-test, *X* is the pretest, *T* is the treatment, *C* is the control condition, *γ* represents the influence of the pretest and the intercept *β_T_* represents the treatment effect.^46^ However, as this model does not address possible carry-over effects of the initial treatment (see Trial design and procedures), we will also include the randomisation (intervention sequence) in the model. Note that the model requires complete data for a given outcome at all four time points. Imputation is not recommended for missing outcomes because the estimation of the model already makes optimal use of the existing data. Secondary analyses will include additional covariates/subgroups such as sex, age, AD stage, history of musical training, general education, music engagement and interventionist’s background training (music therapy vs music education). The role of mediators will be analysed with a series of regression models (as depicted by each arrow in figure 1). Data will be analysed using R (r-project.org). A detailed statistical analysis plan will be developed before the beginning of data analysis.

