## Methods

### Trial design and procedures

Memory for Music (M4M) is a prospective, experimental, crossover, before-and-after, international, assessor-blinded RCT (figure 2). A crossover design allows for comparison within subjects, accounting for effects of covariates and interindividual variation. Compared with a parallel design, a crossover design has the important advantage of obtaining the same statistical power with a smaller sample size. While crossover trials are less common in psychosocial interventions, this design is well suited to our aim: to compare different levels of intensity—minimal versus intensive—of the same musical training approach. The trial does not compare two distinct interventions or test the effect of intervention order but rather evaluates whether increased time and engagement with musical material enhances outcomes. To address potential carry-over, period or sequencing effects,^31^ we have taken the following precautions: (1) a wash-out period of 2 months is included between intervention phases; (2) different musical pieces are used in each phase, ensuring that any observed effects are attributable to training intensity rather than content familiarity and (3) the sequence of interventions (ie, order of interventions) can be included as a covariate in the statistical analysis to account for possible sequence effects.

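### The sequence term is added to deal with carry-over, but in the stated difference model it adjusts for period and leaves carry-over bias in the treatment estimate unchanged

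*Protocol article*

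**What the plan says.** The Statistical analysis section models one quantity per participant, the post-test difference between intensive (T) and minimal (C) training. The covariate is the corresponding difference in pretests, with coefficient gamma, and the intercept is defined as the treatment effect. The section then says that "this model does not address possible carry-over effects of the initial treatment" and, giving that as the reason, adds the randomised sequence to the model. It does not state how sequence is coded, and it names no other statistical handling of carry-over.

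Trial design and procedures lists three precautions against carry-over, period and sequencing effects: a 2-month wash-out, different songs in each phase, and the sequence of interventions, which "can be included as a covariate in the statistical analysis to account for possible sequence effects".

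The Primary outcomes section places ADAS-cog at baseline and at months 5, 7 and 12, so month 7 is the pretest of the second phase.

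**The concern.** The article fixes a method and gives it a purpose that it cannot serve. An analysis plan written from this text would inherit the belief that adding sequence deals with carry-over.

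Carry-over on ADAS-cog is not far-fetched on the article's own account. The Introduction appeals to brain plasticity from musical training, and the Discussion hopes to slow decline. Different songs per phase protect memory for particular songs but not a general cognitive gain, and no reason is given why 2 months of wash-out is enough.

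If intensive training leaves a longer-lasting benefit than minimal training, the intensive-first group does better during its minimal phase. The estimated contrast is then pulled toward zero, and the sequence term does not prevent this.

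There is a second, smaller risk. Once sequence enters the model, the intercept is the average treatment effect only under centred coding.

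**Working it through.** **The plan's own figure.** Inputs from Sample size and power: "aiming for 80% power with a two-sided 5% significance level"; "With a conservative assumption of SD=10"; "the MCID of 3 corresponds to an effect size of d=0.30"; "We further assume a within-subject correlation of r=0.5 between intervention periods"; "an assumed attrition rate ≤20" per cent.
- SD of the within-participant difference: 10·√(2·(1 − 0.5)) = 10.
- Paired t-test for 3 points: 90 completers give 80.4% power.
- 90/0.8 = 112.5, so 113. This reproduces "this leads to a required number of 113 participants to randomise (90 after drop-out".
- The parallel comparator also reproduces: 176 per arm, 352/0.8 = 440.

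**What the sequence term estimates.** Let τ be the treatment effect, π the period-2 minus period-1 effect, and L_T and L_C the carry-over into period 2 after intensive and after minimal training. Lower ADAS-cog is better, so a benefit is negative. Leaving pretests aside for the moment, the mean of Y_T − Y_C is:
- intensive first: τ − π − L_T
- minimal first: τ + π + L_C

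The difference between sequences, which is the sequence coefficient, is −2π − (L_T + L_C). The average of the two, which is the treatment estimate, is τ − (L_T − L_C)/2. Only the difference L_T − L_C biases the estimate. It lies in the average, where a between-sequence contrast cannot reach it.

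**What the pretest covariate does.** Let Lb be the carry-over already present at month 7. With gamma in the model the estimate becomes

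τ − [(L_T − L_C) − γ(Lb_T − Lb_C)]/2.

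The article gives r = 0.5 between periods but no correlation w between pretest and post-test within a phase. With all between-period correlations at 0.5, γ = (w − 0.5)/0.5 = 2w − 1, and the residual SD is 10·√(1 − γ²).
- w = 0.5: γ = 0, SD 10
- w = 0.8: γ = 0.6, SD 8

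**Size.** Assumptions: τ = −3, L_C = 0, 90 completers. The carry-over sizes and w are not in the article.

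| Carry-over at month 7 / month 12 | w = 0.5 | w = 0.8 |
|---|---|---|
| none | −3.00, power 80% | −3.00, power 94% |
| −1.5 / −1.5 | −3 + 0.75 = −2.25, 56% | −3 + 0.75·0.4 = −2.70, 88–89% |
| −3 / −3 | −3 + 1.5 = −1.50, 29% | −3 + 1.5·0.4 = −2.40, 80% |
| −3 / −1.5 (fading) | −2.25, 56% | −3 − (−1.5 + 1.8)/2 = −3.15, 96% |

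Simulated trials with an assumed decline of 0.4 points per month agree to within about 0.04 points and 2 percentage points of power. In them, adding or removing sequence moved the estimate by no more than about 0.04. At w = 0.5, for example, it was −2.23 with sequence and −2.26 without for a carry-over of 1.5, and −1.51 against −1.53 for a carry-over of 3. The sequence coefficient followed the period effect: at w = 0.5 without carry-over it was −5.6, that is −2·2.8.

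**Coding.** The two post-tests, at months 5 and 12, are 7 months apart, so a decline of 0.4 per month gives π = 2.8. With no carry-over and γ = 0, 0/1 coding makes the intercept the effect in the reference sequence only: −3 + 2.8 = −0.2 or −3 − 2.8 = −5.8. With γ = 0.6 the shift is 2.8·0.4 = 1.12, giving −1.88 or −4.12. Centred coding keeps −3.

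**The case against.** The strongest reply is that the model as written includes the pretest difference, and one of those pretests is at month 7. Carry-over visible by then is partly removed. At a within-period correlation of 0.8, power stays near or above 80% even with a persistent 3-point carry-over, and fading carry-over reverses the sign of the bias. This stands. A reader might infer from the algebra that carry-over bias passes through the whole model untouched, or that the trial will be badly underpowered. The article supports neither. The first holds for the sequence term but not for the pretest covariate. The second needs r = 0.5 to apply to every pair of time points, whereas the article assumes it only between periods. Pretest adjustment is still only a partial remedy: carry-over absent at month 7 but present at month 12 stays in the estimate in full.

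The article also names participant as a random effect, which does not fit one difference per participant and may point to a model of the individual scores. There, sequence would be a between-participant contrast that could signal differential carry-over. It still would not remove it from the within-participant treatment estimate.

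Trial design and procedures speaks of sequence effects and does not itself call the covariate a carry-over correction, so it is not an error in its own right. Nor does the article say that it will report a carry-over-adjusted result. Finally, a first-period sensitivity analysis is ordinary content for the detailed analysis plan that the article announces. Its absence here is no fault; it is offered only as part of the remedy.

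**Conclusion.** The point holds for the sequence term. The article gives carry-over as the reason for adding sequence, and in its difference model the term does not have that property: it adjusts for period, with the summed carry-over mixed in. Differential carry-over biases the estimate by the same amount with or without it.

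Under the assumptions tabulated above, persistent carry-over of 1.5 points leaves an estimate of about −2.2 to −2.7 (power 55–88%), and 3 points about −1.5 to −2.4 (power 29–80%), for within-period correlation 0.5 to 0.8. Fading carry-over can slightly over-correct. The documents say nothing about how large carry-over will be, and there is no bias if it is equal in the two conditions. The sample size calculation is not in error, and the sequence term is worth keeping for period adjustment in a progressive disease. This should be fixed; it does not invalidate the design.

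**What to change.** 1. In Statistical analysis, state that sequence is included to adjust for period and does not correct for carry-over. Match the wording in Trial design and procedures.
2. Specify centred coding (±0.5) for sequence, so that the intercept remains the average treatment effect.
3. Prespecify a supportive analysis free of carry-over: month-5 ADAS-cog between the randomised arms, adjusted for baseline and site. Report month-7 scores by sequence descriptively. Base no decision rule on a test for carry-over.

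The cost is a few sentences and one extra analysis of data already being collected. The month-5 comparison is weak. A two-sample t-test with SD 10·√(1 − ρ²) for 3 points gives 37% power at baseline correlation ρ = 0.5 with 45 per arm, and 70% at ρ = 0.8 with 50 per arm. It can therefore support the crossover result but not replace it.

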### Primary outcomes

#### Cognitive outcome: ADAS-cog

Before and after each musical training phase, a neuropsychological assessment battery (ADAScog)^38^ will be administered to all participants by a trained psychometrician blinded to the intervention allocation. The scale consists of items to assess the following domains: language; memory; praxis and orientation. The standard ADAS-cog includes the following 11 subtests, with a total scoring range from 0 (no impairment) to 70 (most severe impairments): word recall (0–10); commands (0–5); naming (0–5); constructional praxis (0–5); ideational praxis (0–5); orientation (0–8); word recognition (0–12); remembering word recognition test instructions (0–5); spoken language ability (0–5); comprehension of spoken language (0–5); word-finding difficulty (0–5). The ADAS-cog score is based on the number of errors made within each subtest. Two versions will be included: one administered at baseline and at the 7-month assessment; another at the 5-month and 12-month assessments. In a retest situation, the minimum clinically important difference (MCID) is 3.^39^ The ADAS-cog takes 30–35 min to administer. The total score of the ADAS-cog at the end of each intervention will be used as the *primary clinical outcome measure*, and the scores on the 11 sub-domains as secondary clinical outcomes. We aim to administer the ADAS-cog within 7 days before the first and after the last musical training session of each intervention phase.

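### The primary model is a complete-case analysis, which conflicts with the plan's all-randomised promise, its efficiency claim and its two opposing statements on imputation

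*Protocol article*

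**What the plan says.** All the relevant statements on missing data are in the Protocol article, section Statistical analysis.

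- **Analysis set.** Outcomes are analysed by intention to treat, defined as "analysing all participants as randomised, regardless of actual participation".
- **Model.** For continuous outcomes the analysis is to "compare the post-test difference between interventions within each participant, adjusted by the difference in pre-tests within each participant". The model is described as hierarchical, and both site and participant are named as random effects. The equation has a single post-test difference on the left and a single pre-test difference on the right. Intervention sequence is added to the model.
- **Data requirement.** "Note that the model requires complete data for a given outcome at all four time points".
- **Imputation, first statement.** "Multiple imputation will be used if attrition is higher than expected".
- **Imputation, second statement.** "Imputation is not recommended for missing outcomes because the estimation of the model already makes optimal use of the existing data".

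The four time points follow from the section Cognitive outcome: ADAS-cog, which describes two test versions, "one administered at baseline and at the 7-month assessment; another at the 5-month and 12-month assessments". The section Sample size and power assumes attrition of at most 20%, with 113 randomised and 90 left after drop-out.

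**The concern.** With one row per participant, a single missing value among months 0, 5, 7 and 12 removes that person. Someone who completes the first randomised period and leaves during the washout contributes nothing, although their month-5 score is a valid randomised comparison. This is a complete-case analysis. It does not literally analyse all participants as randomised.

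The reason given against imputation does not fit this model. It would suit a likelihood-based repeated-measures model that keeps incomplete participants. A model that discards a completed first period does not make optimal use of the data.

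The two imputation sentences also conflict. One is a conditional promise. The other carries no condition, and its stated reason would apply at any level of attrition.

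What is at stake is the validity of the ADAS-cog estimate. Dropout over 12 months in a progressive disease may well relate to decline, and the burden of two sessions per week against one per month could make it differ by sequence.

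**Working it through.** **1. The plan's own sample size.** Inputs from the section Sample size and power: difference 3, SD 10, r=0.5, two-sided 5%, 80% power, 20% attrition.

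- SD of the within-person difference = 10 × √(2 × (1 − 0.5)) = 10, so the standardised difference is 3/10 = 0.30.
- The exact paired t-test needs n = 90 (power 80.4%).
- 90/0.8 = 112.5, rounded up to 113.
- Parallel comparator: 176 per arm, 352 in total, and 352/0.8 = 440.

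All three stated figures (90, 113, 440) reproduce. The 90 is a count of complete participants, so the sizing already matches a complete-case analysis.

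**2. Who is left out.** 113 − 90 = 23, or 23/113 = 20%. If imputation starts only above 20%, all 23 can be excluded without triggering it.

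**3. The statements set side by side.**

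| Statement | Compatible with the four-visit difference model? |
|---|---|
| All participants analysed as randomised | No, for anyone with a missing assessment |
| Optimal use of existing data | No; completed first periods are discarded |
| Imputation if attrition exceeds expectation | Yes, but contradicted by the next row |
| Imputation not recommended | Only as a complete-case rule; its stated reason fails |
| Participant as a random effect | Not separable from the residual with one difference per participant |

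The last row suggests that a long-format mixed model may have been intended. The written equation and the four-visit requirement do not describe one.

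**4. Why bias can arise.** ADAS-cog counts errors, so lower is better. Suppose people with high month-5 scores leave more often. In the intensive-first sequence month 5 is the intensive score, so completers make intensive look too good. In the minimal-first sequence month 5 is the minimal score, so completers make minimal look too good. Averaged over the two sequences, these shifts cancel when dropout is equal. They do not cancel when it is unequal.

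**5. Illustrative size.** Assumptions not in the documents: dropout after month 5 rising with the month-5 score, with the rates by sequence shown below. N=113, SD 10, no true effect, and sequence coded so that the intercept averages both sequences.

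| Dropout, intensive-first vs minimal-first | Complete-case bias, r=0.5 | Complete-case bias, r=0.8 |
|---|---|---|
| 31% vs 11% | about -0.2 to -0.5 points | about -0.1 to -0.2 |
| 22% vs 17% | at most about -0.1 | at most about -0.1 |
| Equal | none | none |

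A negative sign falsely favours intensive training. Against the minimum clinically important difference of 3, 0.2/3 = 7%, 0.5/3 = 17% and 0.1/3 = 3%. A likelihood analysis of all observed visits stayed within about 0.04 of zero, and its empirical SD was about 0 to 4% smaller.

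A separate scenario used a true effect of -3, r=0.5 and about 19% dropout depending on observed change, by the same rule in both sequences (3000 simulated trials). The complete-case estimate averaged -2.93 (SD 1.05) and the likelihood estimate -3.01 (SD 1.03). The bias there was small.

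**The case against.** The strongest reply has four parts.

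- **The imputation sentences can be read as one rule:** impute only above the 20% stated in the sample-size section. A reader might infer that the method will be picked after attrition is seen. The documents do not support that strongly, because a trigger can be read from the text. What stands is that the later rejection has no such condition, and that on this reading up to 20% of participants are still dropped without protection.
- **The larger bias figures come from an extreme scenario.** Dropout of 31% versus 11% averages 21% and exceeded 20% in about 60% of simulated trials, where the conditional sentence would call for imputation. No passage gives dropout by sequence. This stands, so the figures are illustrations and not forecasts.
- **The intention-to-treat definition chiefly separates allocation from session attendance.** A participant who stops sessions but attends assessments stays in. This is fair. The criticism is confined to those lost to assessment, for whom the all-participants wording cannot hold.
- **An analysis plan is still to come.** Leaving detail to it is normal. Here, however, the article states incompatible rules and a reason that is wrong for its model, so an analysis plan must break at least one of them.

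**Conclusion.** The inconsistency is certain from the text. The primary model is complete-case, the optimal-use claim is false for it, and the imputation statements conflict. About 23 of 113 randomised participants would be excluded at the planned attrition.

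Two stronger readings are not supported. A reader might infer that the trial is undersized. It is not: the stated numbers reproduce, 90 completers give 80.4% power, and the efficiency lost is about 0 to 4% in SD. A reader might also infer that the result will be biased by around half a point. That figure needs a nearly threefold dropout difference between sequences, dependence on the month-5 score, and r=0.5. With 22% versus 17% the bias is at most about 0.1 point, and with equal dropout there is none.

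This is a should-fix: the rules are contradictory, the exposure to bias is plausible but of unknown size, and the remedy is cheap.

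**What to change.** State one missing-data rule for the primary analysis. Either of two routes resolves the conflict:

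1. **Preferred.** A likelihood-based repeated-measures mixed model on all observed ADAS-cog assessments, including every randomised participant with any assessment, with period or visit, sequence and treatment effects and with baseline handled in the model. The exact covariance and baseline specification can be settled in the analysis plan.
2. **Alternative.** Multiple imputation at any level of missingness, with no attrition threshold.

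In both cases keep the four-visit difference ANCOVA as a sensitivity analysis, and delete the conflicting imputation sentences and the optimal-use sentence.

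The cost is a change of wording and a slightly more complex model, fitted in R as already planned. No new data or participants are needed. The last outcome assessment is anticipated in October 2027, so the change can be made before outcomes are known.
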